| Objectives: | 
To evaluate the efficacy and safety of EHSG-KF in comparison to meshed STSG in adults and adolescents with partial deep dermal and full-thickness burns.
 
Primary Objective
To evaluate the efficacy of EHSG-KF in comparison to meshed STSG based on:
 
 
Ratio of covered surface area to biopsy site/donor site surface area 4 weeks post grafting
 
 
First Secondary Objective
 
 
% Epithelialization at 3 months post grafting
 
 
Secondary Objectives
To evaluate the safety and efficacy of EHSG-KF in comparison to meshed STSG based on the assessment of:
 
 
Infection
 
Scar quality: 
 
Cutometer® 3, 6, 12, 24 and 36 months post grafting
 
DSM ColorMeter® 3, 6, 12, 24 and 36 months post grafting
 
POSAS-questionnaire 3, 6, 12, 24 and 36 months post grafting
 
 
 
Graft take at 6-10 days post grafting
 
%Epithelialization (to estimate 'time to complete epithelialization') at 3 and 4 weeks, and 2 and 6 months post grafting
 
Incidence of wound closure at 4, 8, and 12 weeks post grafting
 
Growth (% change in surface area, cm^2, between 1 and 3 years post grafting)
 
Assessment and reporting of all observed adverse events
 
QOL assessment (EQ-5D and BSHS-B for patients ≥18 years; EQ-5DY and PedsQL for patients <18 years)
 
Healthcare resource utilization (direct and indirect healthcare costs, this questionnaire will not be handed out to patients)
 
 |

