| Endpoints:  | 
Primary Endpoint
Efficacy evaluation, as a comparison between the EHSG-KF and control sites, based on:
 
 
Ratio of covered surface area to biopsy site/donor site surface area at: 
 
visit 6 (28 ± 3 days post grafting)
 
 
 
 
First Secondary Endpoint
 
 
% Epithelialization at: 
 
visit 8 (90 ± 5 days post grafting)
 
 
 
 
Secondary Endpoints
Safety and efficacy evaluation, as a comparison between the EHSG-KF and control sites, based on:
 
 
Main secondary safety endpoint:
Clinical and microbiologic signs of infection at 
 
visit 4 (6-10 days post grafting)
 
visit 5 (21 ± 2 days post grafting)
 
 
 
Main secondary efficacy endpoints:
Scar quality at the study areas 
 
Assessment of elasticity of the study areas using the Cutometer® at visit 10 (1 year ± 30 days post grafting)
 
 
 
                                                                                                                                                                                                                                                                                                                                                                                                                                                                                                                  |

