#### Management of Poor Graft Take Rate and Slow Epithelialization:

If assessment of graft take at visit 4 (day 6-10 after grafting) shows unsatisfactory results (graft take < 50%), or if assessment of time to complete epithelialisation shows unsatisfactory results (time to complete epithelialisation >8 weeks), the choice of further management is at the Investigators' discretion. According to the management of poor graft take in routine skin grafting, this could mean either conservative management (wound care, dressing changes) until the wound is closed secondarily and healed, or surgical closure by applying the standard of care for this individual situation and patient.

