Studies by Boyce et al. have similarly focused on this endpoint, demonstrating that the requirement for harvesting of donor skin for cultured skin substitutes (CSS) was less than for conventional skin autografts in patients with massive burns. Boyce et al. showed that CSS can be expanded by approximately 67 times, 66 times, and 108 times the area of donor skin, in the 2002, 2006, and 2016 studies, respectively, compared with an estimated value of 4 for 4:1 meshed autograft. In the latter study, the CSS was also shown to substantially reduce mortality when compared to a similar population from the National Burn Repository. The ratio of surface area covered at the experimental area to surface area biopsied, and the ratio of surface area covered at the control area to surface area harvested (i.e. control STSG donor site surface area) will be calculated at Visit 6 (28 ± 3 days post-grafting) and the two ratios will be compared. The covered surfaces areas (cm^2) for both the experimental and control sites will be determined using planimetric analysis at visit 6. Planimetric analysis will be used since the healed areas often have irregular shapes, with dimensions that are not conducive to measurement with a ruler.

In the absence of complications, such as hematomas and associated graft loss, four weeks should allow adequate time for healing of the STSG and EHSG-KF in order to reflect the long-term extent of coverage achieved by the two methods.

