### 10.3.3 Secondary Analyses

In addition to the primary endpoint, all secondary endpoints listed in chapter 6.3 will be evaluated and tested for differences between interventional and standard treatment. The obtained p-values will be interpreted in a strictly exploratory fashion only, and no correction for multiple comparisons will therefore be applied. Statistical analyses for (secondary and exploratory) endpoints measured at multiple timepoints will focus on repeated measure models, to address the dependencies between visits. This will be a Generalized Estimating Equation model in case of binary data, and a mixed-effects model in case of continuous data. If data are not fulfilling underlying model assumptions, a transformation may be necessary before applying the statistical model. Details will be described in the SAP.

### 10.3.4 First Secondary Analyses – Epithelialization at Visit 8

The percentage of epithelialization of a site is the percentage of the grafted area which is closed/healed with dry epithelium, as noted in chapter 8.2.

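### At visit 8 an area that was surgically closed by standard care can be scored as healed by its allocated graft, because the epithelialisation definition does not ask what closed the wound

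*Protocol*

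**What the plan says.** - **Endpoint.** The Synopsis and sections 2.2 and 6.2 set the first secondary endpoint as the percentage of "Epithelialization at 3 months post grafting", read at visit 8 (day 90 ± 5). Section 8.2.1 has the investigator score it subjectively, as a share of the whole grafted area.
- **Definition.** Section 10.3.4: "The percentage of epithelialization of a site is the percentage of the grafted area which is closed/healed with dry epithelium". Neither section separates epithelium that came from the allocated graft from epithelium that came from a later procedure. Wound closure (sections 8.2.1 and 10.3.14) is 100% epithelialisation, so it inherits the definition.
- **Rescue.** The part of section 7.3.5 on poor take and slow epithelialisation has two triggers: take below 50% at visit 4, and "time to complete epithelialisation >8 weeks". Management is then at the investigator's discretion. It may be conservative, or it may be "surgical closure by applying the standard of care for this individual situation and patient". Section 9.7 also foresees re-grafting operations.
- **Follow-up and analysis.** Under section 4.3.2, patients with total loss of EHSG-KF stay in the study until visit 10. Under section 10.3.1, efficacy is analysed in the mITT population as randomised. Section 3.7 requires rescue treatments to be documented in the eCRF.

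**The concern.** Followed literally, the definition credits a standard-care rescue to the graft that failed. The reading then improves when a failed area is re-grafted, which is the opposite of what a measure of graft healing should do. The same applies to closure incidence at visit 8 and to the time-to-complete-epithelialisation analysis in section 10.3.12. At visit 10, the Cutometer and POSAS comparison in an affected pair no longer sets one allocated graft against the other. If a failed EHSG-KF area was closed with a skin graft, part of that comparison is skin graft against skin graft.

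The trial is open label, and investigators both decide on closure and score epithelialisation. Section 10 says the study is also meant to generate hypotheses for phase III, so a 3-month healing estimate that includes rescue without saying so could mislead that planning.

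**Working it through.** **Plan's own figure.** The protocol gives no size or power for this endpoint. Its only sizing figure is 12 evaluable patients for the primary ratio (difference 0.90, SD 1.00, two-sided 5%). An exact one-sample t-test calculation gives 81.0% power at n = 12 and 76.7% at n = 11, so 12 is reproduced. Here it serves only as a denominator.

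**Step 1: timing.** Inputs are the visit windows in section 7.2.1 and the triggers in section 7.3.5.
- Visit 8 window: 90 − 5 = day 85 to 90 + 5 = day 95.
- Eight weeks: 8 × 7 = day 56. From there to visit 8 is 85 − 56 = 29 to 95 − 56 = 39 days (nominal 34).
- Visit 7, the first scheduled visit after day 56, is day 57 to 63. From there to visit 8 is 85 − 63 = 22 to 95 − 57 = 38 days (nominal 30).
- Visit 4 is day 6 to 10. From there to visit 8 is 85 − 10 = 75 to 95 − 6 = 89 days.

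Both triggers fall before the visit 8 reading.

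**Step 2: what is then recorded.** Take an area that meets a trigger and is surgically closed.
- Section 4.3.2 keeps the patient in the study, even after total loss of EHSG-KF.
- Section 10.3.4 counts the closed surface without asking its origin.
- Section 10.3.1 analyses it under the allocated treatment.
- No section scores it as a failure or reports it separately.

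**Step 3: possible size (illustration only).** Let v be the percentage the area would have shown at visit 8 without rescue, and suppose it reads 100% after rescue. One such area among n shifts that treatment's mean by (100 − v)/n points.

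| v | n = 12 | n = 15 |
|---|---|---|
| 70% | 30/12 = 2.5 | 30/15 = 2.0 |
| 50% | 50/12 = 4.2 | 50/15 = 3.3 |
| 30% | 70/12 = 5.8 | 70/15 = 4.7 |

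The second column covers the possible inflation to 15 patients. An area that reads as closed only because of rescue moves visit 8 closure incidence by 1/12 = 8.3 points.

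The values of v and the number of rescued areas are assumptions. If v is taken as the value at the time of rescue, the shift is an upper bound: it assumes complete healing after rescue and no further healing without it.

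**The case against.** **It belongs in the SAP.** Section 10.3.3 defers details of the secondary analyses to the SAP, which is not shown, and a rule for re-treated areas is often placed there. It may exist. However, the protocol itself fixes the endpoint definition, and a SAP that followed it literally would carry the problem forward.

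**As-observed scoring is legitimate.** Counting closure as observed, as randomised, answers a fair question about a strategy of grafting followed by rescue where needed. That stands, and the value should be kept as supportive. The objective, however, is the efficacy of EHSG-KF against meshed STSG, and the protocol does not say that rescue is part of what is being estimated.

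**Failures remain visible elsewhere.** Epithelialisation is also read at visits 5, 6 and 7, photographs are taken from visit 3 on, and rescue treatments are recorded. This is true and limits the harm, but the visit 8 summary would not show it.

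**Stronger readings the documents do not support.**
- *That a re-grafted area will read about 100% at visit 8.* Section 8.1.1 does say that "four weeks should allow adequate time for healing of the STSG and EHSG-KF", but only in the absence of complications such as graft loss. A second graft on a bed that did not close is not that case, and after visit 7 there are only 22 to 38 days, less any time needed to schedule surgery.
- *That the bias favours EHSG-KF.* Rescue is discretionary and open to both areas.
- *That the success claim is at risk through this endpoint.* Success rests on the visit 6 ratio alone. The 8-week trigger comes after visit 6. The visit 4 trigger can precede it, but that concerns the primary ratio and is outside this point.

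**Conclusion.** The point holds as a defect of definition. With both triggers ahead of visit 8, a failed area that was surgically closed by standard care can score as partly or fully healed by its allocated graft, and as closed.

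The size cannot be derived from the protocol. The illustration gives at most 2.5 to 5.8 points per rescued area among 12 for v between 70% and 30%. The direction depends on which area is rescued more often. In the visit 10 scar comparison, re-grafting blurs the contrast in the affected pairs.

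The consequence is limited because all secondary tests are exploratory. A correction is still worthwhile: it is cheap, and the 3-month healing estimate would otherwise be hard to interpret.

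**What to change.** For both study areas and both triggers:

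1. **Sections 10.3.4 and 10.3.14.** Score any surface surgically re-grafted after visit 3 as not epithelialised by the allocated graft, and count the area as not closed from that date. Write this as a single rule. Carrying forward the last value before re-grafting would give a different number whenever partly healed surface is re-grafted, so it should not stand beside it.
2. **Section 10.3.12.** Apply the same rule to time to complete epithelialisation: no closure event is counted after the date of re-grafting.
3. **Supportive result.** Report the as-observed visit 8 value alongside.
4. **Sections 10.3.6 and 10.3.7.** Flag re-grafted pairs in the visit 10 scar analyses and add a sensitivity analysis that excludes them, stating that this exclusion selects on a post-randomisation event.
5. **eCRF.** Record the date and area of re-grafting.

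The cost is a few sentences in the protocol or SAP and two data items, since section 3.7 already requires rescue treatments to be documented. The rule should be fixed before visit 8 results are analysed. The downside is that the visit 8 value may look less favourable. No change to patient care is proposed.

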## 1. Introduction

### 1.1 Background and Rationale

Despite tremendous prevention efforts, burn injuries remain a global health crisis. Eleven million people sought medical attention for burns in 2004, making them the fourth most common type of trauma after traffic accidents, falls, and interpersonal violence. With advances in fluid resuscitation and critical care for burn patients, as well as surgical burn management, mortality rates for major burns have reduced significantly, and the cause of mortality has shifted from early burn shock to delayed multi-organ dysfunction syndrome and sepsis.

With increased survival of patients with extensive burns, clinicians and researchers face the challenge of providing definitive burn wound coverage in the setting of limited skin graft donor sites. The development of alternatives to autologous split-thickness skin grafts has thus become a cornerstone in burn research and could prove to be life-saving and improve quality of life for patients with severe burns.

The current standard of care for the management of deep partial thickness and full-thickness burns is excision of the non-viable burned tissue and definitive coverage with autologous skin grafts. In the developed world, temporary coverage is then typically achieved with cadaveric allograft or, less commonly, with biosynthetic skin substitutes until the patient's condition has stabilized and autologous split-thickness skin graft donor sites are available for harvest to provide definitive coverage. Integra dermal regeneration templates® may also be used for coverage of excised burn defects providing a permanent dermal scaffold onto which a STSG can be grafted, if available, after 3 weeks.

Techniques such as conventional meshing and Meek micrografting allow expansion of autograft to increase the surface area of coverage in the setting of large burns with donor site limitations; however, when compared with non-meshed grafts, these techniques reduce the graft site healing rate, and decrease the area of dermal coverage, thereby compromising graft quality and leading to suboptimal long-term aesthetics and function. Furthermore, autograft donor sites are painful, add to the wound healing burden of the patient, and can themselves lead to complications, such as unfavourable scars.

The introduction of cultured epithelial autografts (CEA) has helped address donor site limitations; however, thirty years since its introduction, CEA continues to yield unacceptable results when used independently for the coverage of deep burns. The considerable problems associated with CEA include graft fragility, susceptibility to infection, poor graft take, propensity of healed grafts towards blistering and breakdown, and, finally and most importantly, unsatisfactory long-term results in terms of both functionality and aesthetics of the reconstituted skin. The clinical introduction of now widely used dermal regeneration templates (e.g. IntegraDRT® and Matriderm®) has pushed the frontiers further, carrying the potential for improved aesthetic and functional results, yet such templates still require coverage with an overlying skin graft.

The evolution of an autologous tissue-engineered skin substitute, which can be used as an alternative to split-thickness skin grafts, represents the next step towards achieving coverage of severe burns with limited donor sites.

In the mid-1990s, the first cultured autologous dermo-epidermal skin substitute, developed by Boyce, was successfully applied clinically for 'compassionate use' in severe burns, and has more recently been investigated in a clinical trial setting. Studies by Boyce et al., have confirmed that the ratio of defect coverage to skin harvested is substantially greater with their

bioengineered skin analogue. However, twenty years later, this skin analogue has still not been brought to market and is not yet available for widespread use. Another bio-engineered dermo-epidermal skin substitute has been introduced in preclinical studies and as a biologic dressing for refractory lower extremity ulcers.

The proposed phase IIb clinical trial aims to evaluate the safety and efficacy of EHSK-KF, a bioengineered autologous dermo-epidermal skin substitute, in adults and adolescents with severe burns, when compared to split-thickness skin grafts (STSG), the current gold standard.

### **1.1.1 Non-Clinical Summary**

The proof-of-principle for EHSK-KF was demonstrated by the grafting of this bio-engineered skin analogue onto full-thickness defects, created surgically, in immuno-incompetent athymic rats and immuno-competent premium pigs. Both animal models showed that the EHSK-KF readily heals full-thickness wounds by regenerating into a fully stratified epidermis supported by an organised and vascularised neodermis. The safety of EHSK-KF was demonstrated with local tolerance (immunotoxicity) and tumorigenicity studies carried out in immuno-competent house pigs and SCID-beige mice, respectively. For further details please refer to the Investigator's Brochure (IB).

### **1.1.2 Clinical Summary**

The present proposal is based on the successful completion of the phase I clinical trial in which EHSK-KF was safely grafted as an autologous skin substitute for the reconstruction of burn scars and congenital nevi, and for the coverage of an acute burn, in 10 paediatric patients.

The primary endpoint was safety, as determined by the rates of local infection and graft take. There were no cases of infection, and graft take was acceptable. The mean graft take rate was 63.5% overall (median 78.0%, range 0-100%, SD 36.5%) and 70.6% (range 5-100%, SD 30.6%) when excluding one patient with 100% graft loss attributable to mechanical disruption of the graft post-operatively. Healed skin analogues have been stable thus far without blistering or breakdown.

There were three adverse events deemed to be possibly related to the study product/treatment. There were three severe adverse events (SAE), one that was deemed to be 'unrelated' to the study product/treatment and two that were deemed to be 'possibly related', but importantly all three of these SAEs are also expected complications of conventional grafting surgery. There were no suspected unexpected serious adverse reactions.

In addition, the healed EHSK-KF yielded high quality scars and excellent tissue elasticity, as supported by the POSAS scores. These findings further substantiate the preclinical animal and laboratory studies, supporting EHSK-KF as a viable skin substitute. The clinical phase of the study took place over two years (June 2014-June 2016), and long-term follow-up assessments were carried out annually for five years post grafting concluding in March 2021. For further details please refer to the IB.

### **1.1.3 Rationale for the Study Product**

As noted above, currently available cell-based products are still plagued with considerable problems. We, therefore, embarked on the "skineering" enterprise in order to develop an autologous dermo-epidermal skin analogue in the laboratory by means of bioengineering.

Over 15 years of laboratory research have been invested in the project of engineering an anatomically near-normal skin analogue. [name] et al. succeeded in growing a hydrogel-based dermo-epidermal construct featuring an epidermal part that will correctly stratify upon grafting, a basement membrane, the characteristic structures of the dermo-epidermal junction, and a close to normal dermis. These grafts, cultured from human cells, were successfully grafted onto immuno-incompetent rats and, thereafter, a large animal

model (pig) allowing grafting of large (7 x 7 cm) laboratory grown autologous skin analogue has been developed. These larger skin substitutes feature not only a near-normal anatomical architecture, but also mechanical properties allowing standard surgical handling, and are an appropriate size for the envisioned application in human patients.

With these preclinical studies successfully carried out, a first series of clinical applications was the next scientifically logical and ethically justifiable step, which started in June 2014 with the inclusion of the first patient in the phase I clinical trial denovoSkin(EHSG-KF)/denovoDerm (KEK-ZH-Nr. 2012-0573, Swissmedic 2013TpP1004). The clinical phase of the study concluded in June 2016 and the 5 year follow-up was completed in March 2021. As noted above, the grafts were applied successfully as autologous skin substitutes in children and young adults. Of note, at the time of grafting, two patients were 18 and 19 years old, demonstrating the successful use of EHSG-KF in young adult patients as well.

The further investigation of this innovative product EHSG-KF may offer great advantages. We feel that the promising results of the phase I clinical trial provide justification to proceed with the phase II clinical trial for EHSG-KF with the primary endpoint reflecting both safety and efficacy. The proposed phase IIb clinical trial will target adult and adolescent patients with severe burns, recognizing the potential benefit of a tissue-engineered autologous skin substitute that is not subject to donor site limitations, for this patient population.

The study will be led from the Zurich area in Switzerland, where there has been a 15 year-long collaboration between laboratory scientists and clinicians, and where the Good Manufacturing Practice (GMP) facility for the manufacturing of EHSG-KF is located, ensuring the best circumstances for the envisioned study.

## 1.2 Investigational Medicinal Product

EHSG-KF is an autologous cellular collagen hydrogel-based graft. The product is classified as a cell-based medicinal product (CBMP) in the US and an Advanced Therapy Medicinal Product (ATMP) in the EU and Switzerland.

It is a viable, tissue engineered autologous dermo-epidermal skin substitute. It is based on a plastically-compressed bovine collagen type I hydrogel seeded with human fibroblasts and overlaid by human keratinocytes (Figure 1). The dosage form of EHSG-KF is a square  $45 \pm 4$  cm^2 graft with a thickness of 0.5 – 2 mm. A more detailed description of EHSG-KF can be found in the IB.

[figure not shown]

**Figure 1: EHSG-KF** is an autologous dermo-epidermal skin substitute based on a plastically compressed collagen type I hydrogel, seeded with autologous dermal fibroblasts and covered by autologous epidermal keratinocytes. A) Schematic view of EHSG-KF; B) Haematoxylin & Eosin staining of EHSG-KF a) before grafting (4x magnification) and b) approximately 90 days after grafting (10x magnification). a) fibroblasts (dark spots) are detectable in the dermal part of EHSG-KF. The epidermal part consists of 1-2 layers of keratinocytes. b) After grafting, fibroblasts are detectable in the dermal part of the biopsy, overlaid by a stratified epidermis, which was established by the thin keratinocyte layer present on top of EHSG-KF.

